#### Visual Analysis

SCED data are primarily interpreted visually [36]. To do so in this study, physical activity and state self-control data will be presented as a time-series graph, with days on the horizontal axis, physical activity or self-control on the vertical axis, and phase changes presented as vertical lines. As recommended by the What Works Clearinghouse guidelines [44,46], we will consider 6 features to examine within- and between-phase data patterns visually: level, trend, variability, overlap, immediacy, and consistency. The phase contrasts to be compared in SCED I are A versus B (baseline with Google Fit only), B versus C (Google Fit only with Google Fit+SCT), and A versus C (baseline with Google Fit+SCT). The phases compared in SCED II are B versus C (Google Fit only with Google Fit+SCT).

Within phases, *level* refers to the mean of all data points in 1 phase and is used to compare changes between phases [36]. *Trend* is the slope of the best-fitting trend line for all data in a phase and is used to determine trends toward (spontaneous) improvement or decline. *Variability* expresses the SD of data about the trend line and is used to calculate the percentage of overlap between data collected in different phases.

Between phases, *overlap* is the proportion of overlap between data from 2 phases, where less overlap indicates stronger intervention effects. The specific nonoverlap index we will use is the Tau-U summary index [76], which is a family of 4 indexes that calculate nonoverlap in relation to the trend. It is expressed by “the percent of data that improve over time considering both phase nonoverlap and Phase B trend, after control of Phase A trend” [76]. Using Tau-U allows for the exploration of, for example, how much the physical activity of a patient has increased after using the SCIPP app while considering a possible increase in physical activity levels that may have already been initiated by Google Fit during the previous phase.

*Immediacy* compares the extent to which the level, trend, and variability of the last and first 3 data points of subsequent phases are discriminably different. In SCED I, immediacy is used to examine whether SCT effects are immediate or cumulative and to make decisions about the appropriate phase length in SCED II. Finally, *consistency* involves examining whether data patterns (level and trend) are consistent in phases with the same condition, where more consistent patterns provide greater certainty for a causal relationship between the intervention and outcome. This will be used in SCED II to examine whether physical activity reaches similar level and trend effects in both B phases (Google Fit only) and both C phases (Google Fit+SCT).

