**Methods:**

A mixed methods approach incorporating 2 single-case experimental designs (SCEDs) and qualitative interviews was used to evaluate and optimize SCT. Overall, 12 participants with SMI will be recruited from 2 organizations offering outpatient and inpatient care to people with SMI. Each experiment will include 6 patients. SCED I is a concurrent multiple-baseline design across participants that explores initial effectiveness and optimal intervention duration. Using accelerometry and experience sampling questionnaires, participants’ physical activity and self-control will be monitored for ≥5 days from baseline, followed by the sequential introduction of Google Fit, the physical activity intervention, for 7 days and the addition of SCIPP: Self-Control Intervention App for 28 days. SCED II is an introduction/withdrawal design in which optimized SCT will be introduced and withdrawn to validate the findings from SCED I. In both experiments, the daily average of total activity counts per hour and the state level of self-control will serve as the primary and secondary outcome measures. Data will be analyzed using visual analysis and piecewise linear regression models.

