### Study Design

This study will be conducted using a series of 2 single-case experimental designs (SCEDs): a concurrent multiple-baseline design across participants (SCED I) [34,35] and an introduction/withdrawal design (SCED II). SCED is a family of high-quality experimental designs that can be used to draw causal inferences about the relationship between the intervention and the outcome [36,37]. In an SCED, the intervention is systematically manipulated across multiple phases of introduction and withdrawal while the outcome variable is measured repeatedly and frequently [36-38]. In this way, individual patients function as their own controls. An overview of both experiments according to the SCRIBE (Single-Case Reporting Guideline in Behavioral Interventions) guidelines [39] is provided in Table 1.

**Table 1 table1:** Single-Case Reporting Guideline in Behavioral Interventions design elements of single-case experimental designs (SCEDs) I and II.

	SCED I	SCED II
Design	Multiple baselines across participants	Introduction-withdrawal
Duration	52 days	Approximately 42 days (28-70 days)
Sequence of phases	A-B-C+follow-up	B-C-B-C
Description of phases	Phase A—baseline: 5 days minimum; no intervention, only monitoring of physical activity and self-control Phase B—Google Fit: 7 days minimum; only Google Fit intervention is administered Phase C—Google Fit+SCT^a^: 28 days minimum; Google Fit and SCT intervention are administered simultaneously Follow-up: 3 days minimum; no intervention, only monitoring of physical activity and self-control	Phase B—Google Fit: 7 days; only Google Fit intervention is administered Phase C—Google Fit+SCT: 7-28 days minimum; optimal phase length is determined from findings of SCED I; Google Fit and SCT intervention are administered simultaneously
Main outcomes	Average TACs^b^ per hour, measured continuously throughout the trial (at least 5 measures per phase) Daily self-control, measured twice daily throughout the trial (at least 5 measures per phase)	Average TACs per hour, measured continuously throughout the trial (at least 5 measures per phase) Daily self-control, measured twice daily throughout the trial (at least 5 measures per phase)
Randomization	Baseline duration is randomized with restriction to have at least 5 baseline observation days and 3 measurements	Not randomized

^a^SCT: self-control training.

^b^TAC: total activity count.

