### Randomization and Blinding

We will randomly assign participants to different baseline, intervention phase B, and follow-up durations in SCED I. All are drawn a priori using the web-based random number generator Research Randomizer [45] with the restriction of having at least 5, 7, and 28 baseline observation days, respectively. In SCED II, phase length will not be randomized as the optimal intervention length will be derived from SCED I. Phase order will not be randomized in both experiments as we are interested in the additive effect of SCT over Google Fit only.

Owing to the nature of the intervention, in which apps are used by participants, it is not possible to blind participants to the phase. The researchers responsible for supporting participants in transferring between phases will not be blinded to the phase for the same reason. Where possible, researchers only involved in data entry, processing, and analysis will be blinded to the phase to improve the reliability of the findings [36].

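### At 7 days of Google Fit against 28 days of Google Fit plus SCT, Tau-U leaves a continuing trend almost uncorrected, contrary to the reason given for choosing it

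*Protocol article*

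**What the plan says.** The Visual Analysis section names the Tau-U summary index as its measure of nonoverlap and describes it as a family of four indexes. It defines the index by a quotation from a cited source: "the percent of data that improve over time considering both phase nonoverlap and Phase B trend, after control of Phase A trend". In that quotation the earlier phase is called A and the later one B. In the study's contrast of interest, the earlier phase is B (Google Fit) and the later is C (Google Fit plus SCT). The contrasts listed for SCED I include "B versus C (Google Fit only with Google Fit+SCT), and A versus C".

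The section then gives its reason for the choice: Tau-U shows how much activity rose after SCIPP "while considering a possible increase in physical activity levels that may have already been initiated by Google Fit during the previous phase".

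The phase lengths for SCED I are in Table 1 (Study Design). Phase B is "Google Fit: 7 days minimum; only Google Fit intervention is administered" and phase C is "28 days minimum; Google Fit and SCT intervention are administered simultaneously". The abstract gives the same 7 and 28 days. Phase B may be longer for some participants: "We will randomly assign participants to different baseline, intervention phase B, and follow-up durations in SCED I" (Randomization and Blinding).

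**The concern.** The primary objective is the effect of SCT added to Google Fit. Google Fit keeps running in phase C, so a Google Fit effect that is still growing, or any other drift over time, carries on across the B-to-C boundary. The protocol tells the reader that Tau-U allows for this.

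Tau-U counts improving pairs of days. Its allowance for trend is the number of improving pairs inside the earlier phase. When that phase is short and the later one long, the allowance is small however steep the trend. The quoted definition also adds improving pairs inside the later phase, so a trend that continues into C raises the score. A reader could then take a high Tau-U as evidence of an SCT effect with the Google Fit trend already accounted for.

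**Working it through.** The protocol states no Tau-U value, so there is no figure to reproduce. The check is whether the index has the stated property at the stated phase lengths.

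**Inputs.** Phase B has 7 days and phase C has 28 (Table 1, both minima). The formula variant is not fixed, so three forms are shown. The documents give neither the slope nor the day-to-day SD of activity. The noise-free figures need neither; the noisy ones assume independent normal noise with SD 1.

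**Pair counts at 7/28.**
- Between phases: 7 × 28 = 196
- Within B: 7 × 6 / 2 = 21
- Within C: 28 × 27 / 2 = 378

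The correction can therefore lower the nonoverlap score by at most 21/196 = 0.107.

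**One straight rising line over all 35 days, no SCT effect.** Every pair improves, so uncorrected Tau is 1.
- Without the C trend: (196 − 21)/196 = 0.893
- With the C trend, denominator 196 + 378: (196 + 378 − 21)/574 = 0.963
- With the C trend, all pairs in the denominator: 553/595 = 0.929

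**Same trend with noise.** For two days d apart and a slope of b SD per day, the expected pair score is 2Φ(bd/√2) − 1. Summing over pairs gives:

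| Drift (SD/day) | Between | Within B | Within C | Uncorrected Tau | Without C trend | With C trend (574 / 595) |
|---|---|---|---|---|---|---|
| 0.05 | 87.6 | 1.6 | 98.4 | 0.447 | 0.439 | 0.321 / 0.310 |
| 0.10 | 139.3 | 3.1 | 174.6 | 0.711 | 0.695 | 0.541 / 0.522 |

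The correction removes 1.6/87.6 and 3.1/139.3 of the score, about 2% in each case. Simulation agrees to within about 0.01.

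**Other phase lengths, noise-free line.**
- Longer phase B. Table 1 gives 52 days in total and minima of 5 + 7 + 28 + 3 = 43, which leaves 9 spare days. B is then at most 16 days if C is 28. The counts are 448, 120 and 378. The scores are 328/448 = 0.732 without the C trend, and 706/826 = 0.855 or 706/946 = 0.746 with it.
- SCED II with a 7-day phase C. The counts are 49, 21 and 21. The scores are 28/49 = 0.571 without the C trend, and 49/70 = 0.70 or 49/91 = 0.538 with it.

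**The planned PLM on the same kind of data.** With trend, level and slope terms at 7/28 and no SCT effect, its level and slope tests each rejected in about 4 to 6% of 3,000 simulated series at every drift from 0 to 1 SD per day. This also assumes independent noise.

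**Detrending first.** One alternative is to remove the phase B Theil-Sen slope from both phases and then compute Tau. Over 4,000 simulated series per setting at 7/28 with no SCT effect, this averages about 0 but has SD 0.78. The ordinary Tau test, with variance 7 × 28 × 36/3 for the pair sum, rejects in about 80% of series, whether or not there is drift. At 16/28 it rejects in about 60%. The ordinary variance ignores the error of a 7-day slope carried across 28 days.

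**The case against.** The strongest reply is that little hangs on Tau-U. Overlap is one of six visual features, and trend is inspected separately. No Tau-U threshold is stated. The only stated significance rule, P<.05, belongs to the PLM, which models trend explicitly. SCED I staggers phase starts by randomising durations, and SCED II withdraws and reintroduces SCT and checks consistency. All of this stands. A reader might infer that drift would end up reported as an SCT effect, or that Tau-U decides the primary question. The documents do not support either reading.

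A second reply is that the large scores are extreme cases. That also stands in part: 0.89 to 0.96 needs a steep or nearly noise-free trend at the minimum phase B length. With modest drift the score is well below the maximum. It is still almost the same as the score with no correction, and that is the point at issue.

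A third reply is that the variant is not fixed, that the word control appears only inside a quotation, and that the study's own sentence is softer. But every trend-corrected form was tried and none removes the trend. The sentence on Google Fit is the protocol's own reason for its choice.

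The PLM does not repair the statement. The protocol calls the PLM a supplement and says that SCED data are interpreted mainly by eye. If a high Tau-U met a null PLM, the text as written would tell the reader that Tau-U had already taken the Google Fit trend into account.

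**Conclusion.** The stated property is wrong at the planned phase lengths. At 7/28 the correction is capped at 0.107 and in realistic noise removes about 2% of the score. Forms that add the C trend count a continuing rise in favour of SCT. The cap follows from the phase lengths alone. The noisy figures rest on assumed slopes and independent errors.

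On a noise-free line the problem is smaller with a longer phase B (0.73 to 0.86 at 16/28) or a 7-day phase C in SCED II (0.57 without the C trend), but it does not disappear. It is a fault in the justification and reading of one index. It does not show that the study's conclusion on SCT would be wrong, because the PLM and the design features offer protection against smooth drift.

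**What to change.** In the Visual Analysis section:
- Withdraw the statement that Tau-U takes account of an increase begun by Google Fit.
- Report plain between-phase Tau, without the phase C trend, as a descriptive overlap index only.
- State that any conclusion about SCT over Google Fit net of trend rests on the B-to-C level and slope terms of the PLM already planned.

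A Theil-Sen-detrended Tau with its ordinary interval should not be used instead, given the rejection rate of about 80% under no effect.

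The cost is a few sentences and no new data or analysis. The downside is precision, because the phase B trend comes from few days. At 7/28 with independent noise, the standard error of the slope change is √(1/28 + 1/1827) = 0.19 SD per day, where 28 and 1827 are the sums of squared day deviations within B and C. That of the level change at the first day of C is √(1/7 + 4²/28 + 1/28 + 13.5²/1827) = 0.92 SD. The report should show these intervals, so that a null PLM result is not read as evidence of no SCT effect.

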### Study Objectives

Therefore, this study further explores a mobile SCT app and the assumption that it can be used to bolster the effectiveness of existing physical activity interventions. It does so specifically in the vulnerable population of people with SMI. The primary objective is to assess the effect of adding a mobile SCT app to a mobile lifestyle intervention aimed at increasing physical activity (Google Fit) on physical activity levels in people with SMI. The secondary objective is to examine the effect of this combined intervention on self-control directly. Finally, we will explore how long SCT should be offered to produce beneficial outcomes on physical activity and whether and which individual characteristics of patients influence SCT effects.

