There are several reasons for using SCED to evaluate interventions in people with SMI. First, SCEDs require only a small number of participants—typically 3 to 6. This makes it more feasible to recruit a sufficient number of participants and requires less time and financial resources from both staff and patients. Furthermore, SCEDs can handle heterogeneous samples as participants function as their own controls. This makes it possible to involve the diverse population with SMI, who may present with comorbidities and a broad range of psychosocial problems. Finally, SCEDs enable research into the working mechanisms of SCT, which is required [25] but nearly impossible to achieve through a randomized controlled trial (RCT) as an intervention is treated as a coherent whole, making it hard to open the black box of the studied intervention [40]. Overall, this makes SCEDs very suitable for the evaluation of interventions [41,42] and an excellent and feasible alternative to classic experimental designs such as the RCT.

In total, 2 SCED experiments are used to address different aspects of the overall research aim. SCED I is used to (1) determine the initial effectiveness of the intervention, (2) explore for which patients SCT may be most effective, and (3) determine how long SCT should be offered for optimal effects. The design of SCED I is A-B-C+follow-up, where A refers to the baseline phase, B is the physical activity intervention alone (Google Fit), and C is the combination of physical activity intervention+SCT intervention, followed by a follow-up in which patients are monitored but no interventions are administered. In addition, SCED I uses a mixed methods design incorporating qualitative interviews to provide insights into patients’ experiences with both the mobile SCT app and the participation in an extensive longitudinal study. To explore the onset and duration of SCT effects on self-control, SCT is offered for 4 weeks instead of the customary 2 weeks [43]. This information will be used to determine whether SCT should be offered 1, 2, 3, or 4 weeks in SCED II.

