### Data Analysis

#### Overview

Data analysis will include both visual and supplementary statistical analyses of the time-series data for both SCED I and II [36,42]. Data analysis will be performed using Microsoft Excel (Microsoft Corp), the web-based Tau-U calculator accessible via Single Case Research [72], and R (version 1.4; R Foundation for Statistical Computing) [73] and separately for the primary and secondary outcomes.

To prepare the data for analysis, we will score the primary outcome of physical activity as the daily average of total activity counts per hour. The secondary outcome of daily self-control will be scored as the daily average of the 4 self-control items. Next, we will use the median average deviation to identify and remove outliers. The median average deviation uses the median to identify scores that deviate 3.5 times from the median as outliers using a 95% CI. It is specifically recommended for use in small-sample studies, including SCEDs [74].

As both experiments collect continuous data that are averaged on a daily level, our missing data approach primarily consists of making full use of data that are available. To illustrate, self-control will be measured in the morning and evening. If the morning data are missing, the afternoon data will be used to calculate the level of self-control for that day. If no data are available on a given day, we will use multiple imputation to impute missing data. Multiple imputation methods have recently been developed specifically for use in SCED studies and have several advantages over other missing data approaches, including retention of collected data, maintenance of the design structure of an SCED, reduction of bias, and the ability to capture and communicate uncertainty regarding imputed scores [75].

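### The only analysis feature tied to choosing 1, 2, 3 or 4 weeks of SCT for SCED II is immediacy, which looks at the first 3 days of phase C and cannot separate these options

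*Protocol article*

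**What the plan says.** Study Objectives sets an exploratory aim on duration: "we will explore how long SCT should be offered to produce beneficial outcomes on physical activity". Study Design explains the long SCT phase: "To explore the onset and duration of SCT effects on self-control, SCT is offered for 4 weeks instead of the customary 2 weeks". It continues: "This information will be used to determine whether SCT should be offered 1, 2, 3, or 4 weeks in SCED II". Table 1 says only that the SCED II length comes from the SCED I findings, within a range of 7 to 28 days.

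The analysis that serves this decision is named once, under Visual Analysis: "immediacy is used to examine whether SCT effects are immediate or cumulative and to make decisions about the appropriate phase length in SCED II". The sentence before it defines immediacy as a feature that "compares the extent to which the level, trend, and variability of the last and first 3 data points of subsequent phases are discriminably different".

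A data point is one day. The Data Analysis overview gives the unit ("As both experiments collect continuous data that are averaged on a daily level"), and the graphs are drawn "with days on the horizontal axis, physical activity or self-control on the vertical axis, and phase changes presented as vertical lines". The contrast at the start of SCT in SCED I is B versus C.

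**The concern.** All four candidate durations end on day 7 of phase C or later, but the immediacy window closes on day 3. Days 4 to 28, which SCED I was lengthened to collect, do not enter the one feature assigned to the decision. If immediacy says that the effect is not immediate, it gives no indication of which week to choose.

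The article's own theory adds to the difficulty. The Introduction describes a strength model in which exerting self-control may cost something in the short term and builds capacity only with repeated use. The first 3 days are therefore where benefit is least expected.

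Determining the duration is one of three listed purposes of SCED I, and the main aim of SCED II is to validate an intervention optimized partly on duration. A length chosen on uninformative evidence would be carried into SCED II as the optimized one.

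**Working it through.** **The plan's own figure.** Table 1 gives SCED II as approximately 42 days (28-70). With sequence B-C-B-C and B = 7 days, the total is 2 x (7 + C). For C = 7, 14, 21 and 28 this gives 28, 42, 56 and 70 days, so the range reproduces and the four options are as stated.

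**Share of the data used.** Immediacy at the B-to-C change uses 3 of 28 phase C days: 3/28 = 10.7%.

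**Without noise.** Take effect curves that share their first 3 days (1/28, 2/28 and 3/28 of the plateau) and then rise to the plateau at day 7, 14, 21 or 28. The immediacy level contrast is (1 + 2 + 3)/(3 x 28) = 0.071 of the plateau for all four. If the effect begins only after day 3, the contrast is 0 for all four. No amount of data within that window would tell the options apart.

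**With noise, in a case kinder to immediacy.** Assumptions, none from the documents: the effect rises linearly to its full size over k days, the full effect is 1 daily SD (s), days are independent, and 6 patients are averaged.

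- Immediacy contrast: mean of days 1-3 = 2/k, that is 0.286, 0.143, 0.095 and 0.071 s for k = 7, 14, 21 and 28.
- Separation of k = 14 from k = 28: 0.143 - 0.071 = 0.07 s.
- SE of a 3-day against a 3-day mean: sqrt(2/3) = 0.82 s for one patient; divided by sqrt(6), 0.33 s.
- Week 2 of phase C (days 8-14, mean day 11): 11/14 = 0.786 s for k = 14 and 11/28 = 0.393 s for k = 28. Separation: 0.39 s.
- SE of a 7-day against a 7-day mean: sqrt(2/7) = 0.535 s; divided by sqrt(6), 0.22 s.

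The separation is about 0.2 SE by immediacy (0.07/0.33) and about 1.8 SE by the week 2 mean (0.39/0.22).

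**Simulation on the same ramps**, with shape and height taken as known, averaging 6 patients at a 1 SD plateau. Immediacy picks the right one of four durations in 31% of runs, against 25% by chance. The full 28-day series picks it in 80% if the phase B level is treated as known. A rerun that estimates the phase B level from 7 noisy days gives 69%. The second figure is the fairer comparison, because immediacy also carries phase B noise.

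**Other planned features.** Trend is one best-fitting line per phase, and the piecewise linear model (PLM) has one slope change per phase. Both use all 28 days, but a single straight line does not show where a curve flattens. A C-versus-follow-up immediacy contrast, which is not listed, would add only days 26-28. On the linear ramps these stand at 1.0 of the plateau for k = 7, 14 and 21 and at 27/28 = 0.964 for k = 28.

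**The case against.** The strongest reply is that the article nowhere makes immediacy the only criterion. Study Design says that the course over 4 weeks informs the choice, Table 1 refers to SCED I findings in general, and every day is plotted, so an analyst could see a plateau by eye. This stands in part. A reader might infer that the duration will be picked from 3 days of data alone and is therefore noise; the text does not support that. It remains true that immediacy is the only feature linked to the decision and that the planned line-based summaries would not locate a plateau.

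A second reply is that a decision rule is detail that an article may leave to a fuller document. That would answer a complaint of omission. Here a method is stated, and it cannot answer the question put to it.

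A third is that the duration aim is exploratory and SCED II has its own B-versus-C comparison. This stands. A reader might infer that a badly chosen length would invalidate SCED II. It would not: each candidate length exceeds the 5-point minimum, and the contrast is made within SCED II.

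Finally, a reader might see a contradiction between Study Objectives, which ties duration to physical activity, and Study Design, which ties the 4-week extension to self-control. One states an aim and the other a reason for the phase length, and the two outcomes are analysed separately. This is an ambiguity about which outcome governs the choice.

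**Conclusion.** The point holds as a mismatch between a stated method and its purpose, and should be fixed. Immediacy can help to tell an immediate from a delayed effect; it cannot tell 1, 2, 3 and 4 weeks apart. That conclusion rests only on the definition of immediacy and the daily time unit.

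The sizes (0.07 s with SE 0.33 s, against 0.39 s with SE 0.22 s) are illustrative. They rest on a linear build-up, a 1 SD effect and independent days. Positive serial correlation would widen both standard errors. The likely cost is a poorly founded phase length in SCED II, not an invalid SCED II.

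**What to change.** Under Visual Analysis, keep immediacy as a descriptive check on immediate versus delayed onset, and say that the SCED II duration is based on the whole phase C series. Two workable forms are:

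- week-of-C effects (weeks 1 to 4, each against phase B) in the SCED I multilevel PLM, with serial correlation allowed;
- a plateau or change-point model.

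Either should be shown with intervals.

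Before SCED I is analysed, state which outcome governs the choice (physical activity or self-control) and the rule that turns the estimates into a duration. Check the rule by simulation first, since simple rules can misbehave. For example, taking the first week that reaches 80% of the largest weekly effect selects weeks 2, 3, 3 and 4 on noiseless linear build-ups of 7, 14, 21 and 28 days. It never selects week 1 and does not separate 14 from 21 days.

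The cost is a few model terms, a short simulation and some added text; no new data are needed. With 6 patients the weekly estimates will still have wide intervals, and the report should say so. The choice of duration itself remains with the sponsor.
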